**Fig. 1 Fig1:**
[figure not shown]
Sample size required for given correlation coefficient

### Data analysis and modelling

This study will summarize ANC1 participant demographic characteristics using descriptive statistics for age and gravidity by health facility and district. Key indicators will include:Total women attending ANC1, and proportion enrolled in ANC1 surveillance.Mean age of enrolled women (years; mean, 95% CI).Number enrolled by gravidity (n, %) by gravida 1, gravida 2, and gravida 3 + .

Prevalence is calculated as the number of women with positive RDT results divided by the total number of women tested [11]. Within each health facility and district, prevalence will be disaggregated by gravidity relative to the current pregnancy (i.e., first pregnancy [gravida 1], second pregnancy [gravida 2], and third or more pregnancy [gravida 3 +]). The monthly malaria prevalence data will be used to produce time series graphs, quarterly and/or annually, for correlation with cross-sectional survey estimates. In addition, where available, the proportion of RDT-positive women who are asymptomatic and symptomatic will be calculated.

To compare ANC1 malaria prevalence to prevalence from cross-sectional surveys within the same district, ANC1 malaria prevalence are obtained for the three months surrounding the community cross-sectional surveys (i.e., the month before the cross-sectional survey, the month of the survey, and the month directly following the cross-sectional survey). The relationship between malaria prevalence at ANC1 and in the community will be quantified using mixed-effects logistic regression, accounting for likely modifiers such as age, gravidity, transmission intensity, and transmission season, and adjusting for sampling effort in time and space. To quantify the incremental value of the ANC1 data, the ability of the ANC1 data to predict population prevalence using these models will be tested using leave-one-out cross-validation for each district and compared to alternative predictive models in the absence of any ANC1 data (e.g., extrapolating district-level trends from other districts sampled within the region). With support of national malaria control programmes and operational partners, district-level data on the temporal distribution of interventions within each region will be leveraged to assess the utility of ANC1 data to capture plausible trends in intervention impact. Similar analyses will be conducted to quantify the relationship between the cross-sectional surveys, the ANC1 data, reported case incidence, and the malaria test-positivity rate (obtained by dividing the number of positive malaria tests by the number of tests performed). In addition, the use of more heuristic measures such as the Kendall correlation coefficient, which provides a summary of the extent to which prevalence ranking of each district remains constant over time [12], will be used to assess the extent to which the choice of malaria metric influences operational decision-making.

Estimates of care-seeking behaviors and indicators for bed net ownership, use, and access will be determined for ANC1 data and compared to the corresponding indicators from the cross-sectional surveys. Net use and ownership (proportion of households that own at least one bed net and proportion of households with one net for every two people) will be aggregated monthly for each sampling unit/district and correlated with monthly ANC1 malaria prevalence to compare trends.

Once an optimal predictive model of community prevalence using ANC1 data has been obtained, this relationship will be incorporated within an existing, well-established mechanistic model of malaria transmission [17–19] in an attempt to provide a framework that can convert estimates of ANC1 malaria prevalence into continuous measures of community malaria transmission and burden with which to explore future intervention scenarios (analogous to a current framework that involves calibrating to cross-sectional data [20]).

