**Results:**

This study will assess malaria prevalence at ANC1 aggregated at health facility and district levels, and by gravidity relative to current pregnancy (i.e., gravida 1, gravida 2, and gravida 3 +). ANC1 malaria prevalence will be presented as monthly trends. Additionally, correlation between ANC1 and household survey–derived estimates of malaria prevalence, bed net ownership and use, and care-seeking will be assessed.

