**Conclusion:**

ANC1-based surveillance has the potential to provide a cost-effective, localized measure of malaria prevalence that is representative of the general population and useful for tracking monthly changes in parasite prevalence, as well as providing population-representative estimates of intervention coverage and care-seeking behavior. This study will evaluate the representativeness of these measures and collect information on operational feasibility, usefulness for programmatic decision-making, and potential for scale-up of malaria ANC1 surveillance.

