### Secondary outcomes

Comparison of ANC1 data to cross-sectional household survey data to ascertain whether pregnant women attending ANC1 can be a sentinel population for estimating, both overall and by gravidity:Bed net ownership and use the previous night.Population access to bed nets (proportion of households achieving one net for every two people).Care-seeking behaviour for malaria.Reported acceptability and feasibility of ANC1 malaria surveillance to women and providers.Relationship between ANC1 malaria prevalence and malaria case incidence derived from DHIS2 (where population denominator data are available).

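### Correlation, the only measure named for comparing ANC1 with survey net and care-seeking coverage, cannot show that ANC1 coverage is representative in level

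*Protocol article*

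**What the plan says.** **Aim.** The Abstract (Conclusion) describes ANC1 surveillance as having the potential for "providing population-representative estimates of intervention coverage and care-seeking behavior", and then says that the study will evaluate how representative these measures are. Secondary outcomes sets up a comparison with household survey data "to ascertain whether pregnant women attending ANC1 can be a sentinel population for estimating, both overall and by gravidity". The list that follows includes "Bed net ownership and use the previous night", access to nets, and care-seeking for malaria.

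**Comparison with the survey.** Data analysis and modelling says that the ANC1 estimates of care-seeking and of net ownership, use and access will be "compared to the corresponding indicators from the cross-sectional surveys". It does not say by what measure. The Abstract (Results) does: "correlation between ANC1 and household survey–derived estimates of malaria prevalence, bed net ownership and use, and care-seeking will be assessed".

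**Added trend analysis.** The next sentence of Data analysis and modelling says that net use and ownership will be "aggregated monthly for each sampling unit/district and correlated with monthly ANC1 malaria prevalence to compare trends". The indicators are given in a bracket as "proportion of households that own at least one bed net and proportion of households with one net for every two people".

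**The concern.** Study design says that ANC1 women and households answer similar questions, so both sources give proportions on the same scale. A representative estimate of coverage is then one whose level agrees with the survey, and that can be measured directly. Correlation measures something else: whether areas with higher survey coverage also have higher ANC1 coverage. If ANC1 women differ from households by about the same amount everywhere, correlation does not register it.

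Such a shift is plausible on the document's own account. Study limitations names selection through non-attendance, private clinics and poor access. Background puts average attendance at 72%. Women who come to a clinic may also differ in care-seeking, which is one of the indicators to be validated.

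For malaria prevalence, the analysis section adds regression and leave-one-out prediction to the correlation. It states no counterpart for coverage. A high correlation could therefore be read as support for representative coverage even though the levels differ by an amount that matters to a control programme.

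**Working it through.** **1. The plan's own figures.** Both sample-size figures reproduce.

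- Facilities for a correlation of 0.6 (two-sided alpha 0.05, 80% power), by Fisher's z: n = ((1.960 + 0.842)/atanh(0.6))² + 3 = 19.3, so 20.
- Women per month: n0 = 1.96² × 0.25/0.10² = 96.04. With the finite population correction for 1,000, n = 96.04 × 1,000/(96.04 + 999) = 87.7, so 88.

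The first sizes a correlation and the second the interval for one proportion. Neither sizes the agreement of two coverage estimates.

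**2. Correlation under a constant offset.** Let S be survey coverage in an area and ANC1 coverage A = S + b. Adding a constant changes neither the variance nor the covariance, so r = 1 for every b. Lin's concordance does respond: CCC = 2v/(2v + b²), where v is the variance of S. Assumption, not in the documents: S is spread evenly over 30% to 80%, so v = 0.5²/12 = 0.02083 and 2v = 0.04167.

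| Offset b | r | CCC |
|---|---|---|
| 10 points | 1.00 | 0.04167/(0.04167 + 0.0100) = 0.81 |
| 15 points | 1.00 | 0.04167/(0.04167 + 0.0225) = 0.65 |
| 20 points | 1.00 | 0.04167/(0.04167 + 0.0400) = 0.51 |

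The CCC values depend on the assumed spread. The result r = 1 does not.

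**3. The net-malaria correlation.** Both of its series come from ANC1, so it cannot show how ANC1 coverage relates to household coverage. Season may also drive it. Suppose each series is a yearly sine wave of amplitude a plus independent noise with SD s, and the waves are offset by an angle φ. Then r = (a²/2)cos φ/(a²/2 + s²). With s = 5 points (all values assumed):

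- a = 10, in phase: 50/(50 + 25) = 0.67; in anti-phase: −0.67.
- a = 5, in phase: 12.5/(12.5 + 25) = 0.33.
- A quarter-year apart: 0.

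The value thus runs from −0.67 to 0.67 with no link between nets and malaria beyond the calendar. The documents give no seasonal amplitudes, and ownership and access may vary less by season than use. This is a caution about interpretation, not a forecast.

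**4. What an agreement analysis could resolve.** Inputs: 88 women a month (Sample size) over the three-month window stated for prevalence, so 3 × 88 = 264; survey sizes of 190 per district in Burkina Faso and 420 per district or local government area in Mozambique and Nigeria (Table 1). Assumptions: p = 0.5, no design effect for ANC1, and a survey design effect D of 1 or 2. Half-width = 1.96 × √(0.25/264 + 0.25 × D/n).

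| Survey n | D = 1 | D = 2 |
|---|---|---|
| 420 | 7.7 points | 9.1 points |
| 190 | 9.3 points | 11.7 points |

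A 20-point difference would show in a single district. A 10-point difference would be marginal, and at n = 190 with D = 2 it lies inside the half-width.

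**The case against.** The strongest reply is that the analysis section does plan a like-for-like comparison. The sentence just before the net-malaria correlation sets ANC1 indicators beside the corresponding survey indicators. A reader might infer that malaria prevalence has taken the place of the survey indicator. The text does not support that: the correlation with prevalence is an addition, is labelled a comparison of trends, and covers net indicators but not care-seeking. This stands.

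Nor has net use been dropped, as the bracket might suggest. It remains among the secondary outcomes, in the planned survey comparison and in the data to be collected. Only the definition in that sentence is incomplete.

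A third reply is that an article may leave the measure of comparison to a fuller plan, and that Objectives speaks of coverage only in terms of monitoring trends. An unnamed measure would indeed be no finding. But the abstract does name one for coverage, and it is unsuited to the question in the Abstract (Conclusion) and in Secondary outcomes, which goes beyond trend.

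Finally, no rule says that representativeness will be declared from r alone, and the documents do not establish the size or direction of any coverage bias. Attending routine antenatal care is not the same as seeking care for fever. Both points stand, so the offsets above are illustrations only.

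**Conclusion.** The point holds in a limited form. The coverage aim concerns level, the only measure named for it is correlation, and correlation is blind to a constant difference of any size. That is exact and needs no assumption. The concordance values of 0.81 to 0.51 rest on the assumed spread of coverage, and the seasonal values on assumed amplitudes, noise and phase.

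The net-malaria correlation can describe trends but cannot support representativeness, and its bracket does not match the net-use outcome. The documents do not show that ANC1 coverage is biased, or that the survey comparison has been abandoned. This is an improvement worth making because it is cheap and answers the question asked; it is not a flaw that undermines the study.

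**What to change.** - For each indicator (net ownership, use, access and care-seeking), pair the ANC1 and survey estimates for the same unit over the month before, the month of and the month after the survey.
- Report the ANC1-minus-survey difference with its 95% CI, and the limits of agreement across units, overall and by gravidity.
- Base any statement on representativeness on these results, with correlation secondary. Word the abstract and the analysis section alike.
- Complete the bracket in Data analysis and modelling so that net use means use the previous night, as in Secondary outcomes.
- Keep the monthly net-malaria comparison descriptive, or adjust it for calendar month.

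The cost is a little more analysis and some rewording; no new data are needed. The intervals for single districts will be visibly wide, about 8 to 12 points either way under the assumptions above, and wider if ANC1 clustering by facility is allowed for.

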### Data management

Data will be obtained from separately generated electronic or paper registers in each country. At each health facility, teams will be trained to conduct data quality assessments to monitor and improve data quality and completeness. Health facility–level ANC1 data from the DHIS2 system will include the monthly number of ANC attendees, the number tested for malaria at ANC1, and the number positive for malaria. Additional data will be collected on maternal age, gravidity, and insecticide-treated net ownership and utilization. Data on malaria prevalence among children will be obtained from representative, cross-sectional, household surveys as specified in the parent studies. Participants will be assigned a unique identifier number by the study, and will be identified only by this number in the dataset. No participant names or other information that would make the participant identifiable will be included.

### Consent

Individual written consent is obtained from women of legal age prior to testing and questionnaire administration during ANC1. In Mozambique and Nigeria, women under legal age are able to participate with the consent of their parent or legal guardian. Participants are told the general purpose, possible risks, and benefits of the ANC1 pilot surveillance activity in the local language. Participation is voluntary.

### Ethical clearance

Ethical clearance for the study was sought and obtained from the following institutional review boards:Comité d’Ethique de La Recherche de l’ISBA, Institut des Sciences Biomédicales Appliquées (Benin).PATH Research Ethics Committee (Burkina Faso, Mozambique, Zambia).Centre National de Recherche et de Formation sur le Paludisme (Burkina Faso).Comité d’Ethique pour la Recherche en Santé (Burkina Faso).Comité Institucional de Bioética para Saúde (Mozambique).National Health Research Ethics Committee of Nigeria (Nigeria).World Health Organization Research Ethics Review Committee (Nigeria).Medical Research Coordination Committee of the National Institute for Medical Research (Tanzania).National Health Research Ethics Committee (Zambia).

In addition, this activity was reviewed by CDC and was conducted consistent with applicable federal law and CDC policy.

## Discussion

This work builds on previous work assessing the validity of using pregnant women attending ANC1 as a sentinel population for monitoring malaria prevalence over time [10, 12]*.* In the present expanded observational study, ANC1-based surveillance collects additional data on indicators of bed net access and use and care-seeking behavior, information that is not collected in routine HMIS settings. The results generated from this study will be used to validate how reliably data collected during routine ANC visits can be used for malaria surveillance in malaria-endemic regions of sub-Saharan Africa.

### Public health importance of ANC-based malaria surveillance

In sub-Saharan Africa, approximately 72% of pregnant women attend ANC at least once during pregnancy [3], even in many rural areas where health care is not easily obtained. Malaria prevalence estimates from ANC1 attendees (before administration of IPTp) could, therefore, prove useful for monitoring changes in malaria transmission over time. ANC1-based surveillance could provide real-time, weekly or monthly data on malaria trends as well as information on access to control interventions such as ownership and use of insecticide-treated bed nets at the district and health facility level, which is sometimes missed in routine HMISs. Subtle changes in trends like early epidemics may be detectible, allowing more timely responses from malaria control programmes.

ANC1-based surveillance offers a basis for targeting malaria control interventions and resource allocation depending on local transmission levels [11]. As malaria transmission continues to decline and infections become more heterogeneous [21] in some settings, ANC1-based surveillance can be used as an adjunct for malaria elimination activities by identifying foci of residual transmission not captured by case-based passive surveillance or cross-sectional surveys. Where funding is available, molecular analysis of *Plasmodium* isolates from pregnant women may characterize genetic signatures of malaria transmission intensity, anti-malarial resistance, and detection of deletions of antigens targeted by RDTs [22, 23] in a way that is easily obtained yet representative of the general population.

### How results will be used

Routine malaria testing of all ANC1 attendees irrespective of symptoms potentially improves pregnancy outcomes by testing and treating women with asymptomatic but detectable parasitaemia. The results generated will add to existing knowledge and evidence that supports use of women attending ANC1 as a pragmatic sentinel (Additional file 1) population for malaria surveillance. The present study will continue to expand the evidence base generated by studies characterizing the relationship between malaria infection in pregnant women and in children in the same communities [9] across new locations and various transmission settings. Geospatial and temporal mapping of infection prevalence by village and/or health facility may also reveal specific hot spots [11].

### Challenges

ANC1-based surveillance requires strengthening systems for routine data collection and changing data management and reporting procedures, as ANC registers would need to include additional fields such as questions on insecticide-treated net use and care-seeking, which are not typically recorded. Routinely aggregated data such as women’s age and gravidity would need to be included at an individual level to optimize analysis of prevalence trends. To be most useful, data would need to be collected and reviewed in near real-time, which can be a challenge. Scaling ANC1-based surveillance requires investment in the capacity of midwives, which would involve training on revised policy guidelines to test and treat all women, increasing the number of midwives to support malaria testing, and/or identification of other cadres of workers who can assist in collecting this information. While theoretically, universal malaria testing at ANC1 could increase the duration of the appointment or disrupt patient flow, studies assessing the feasibility have not found this to be the case [24–27]. Increased funding would be required to ensure that health facilities have sufficient RDTs for universal testing and to avoid stockouts of antimalarial treatments. Funding would also need to support modification of HMISs to distinguish between positive infections in women being tested routinely at ANC1 from symptomatic pregnant women tested during unscheduled visits or those later in pregnancy.

### Study limitations

Using ANC1 for malaria surveillance depends on the extent to which pregnant women attend public ANC clinics, which is affected by nonattendance or attendance at private ANC clinics, among other factors. In countries where attendance at private ANC clinics is high, or if variations exist among rural and urban areas, underrepresentation of private clinics in the surveillance system could introduce selection bias if populations of pregnant women attending private and public ANC clinics differ with regard to malaria exposure [15]. Because private facilities are more commonly located in urban settings, where malaria risk is generally lower, ANC1 data may not be fully representative of the population. Similarly, areas with poor access to health facilities in general may be more likely to be rural and have higher malaria prevalence; this could induce bias if women who present for care are in the areas with lower prevalence. Additionally, bias may arise at screening, particularly if RDTs are limited, if symptomatic women are preferentially tested. Finally, while health facilities have defined catchment areas, people may, to varying extent, choose to seek care outside of their defined health facility. Defining catchment areas strictly is a complex task for many surveillance indicators [28], including malaria case metrics [29]. As data are aggregated upward to larger areas, i.e., districts rather than specific health facility catchments, the effect of people’s movement is likely diminished. To better account for movement of people outside of their designated catchment areas, one could collect data on where people reside; this was done in Zambia where it was recognized that many of the women seeking care in border facilities might have crossed over from Mozambique, allowing for exclusion of these women from the comparison with the household survey data.

## Conclusions

ANC1-based surveillance offers the potential of a lower-cost, more granular, and potentially more representative measure of community malaria burden and other indicators typically sought through cross-sectional surveys. While there are numerous potential benefits of this method of malaria surveillance, it needs to be rigorously validated across a range of settings, particularly with respect to measuring coverage indicators for malaria control measures. As with many routine data collection efforts, post-validation challenges would remain, not the least of which would be ensuring adequate stock of commodities, expanded training requirements, register modifications, and policy changes.

## Data Availability

The datasets used and/or analysed during the current study are available from the corresponding author on reasonable request.

